### Statistical analysis

Primary analyses will follow an intent-to-treat approach such that patients will be analyzed based on the group to which they were initially randomized after exclusion of patients with infection ruled out during their hospitalization. We will assess the balance in the distributions of baseline covariates for patient factors (e.g., age, comorbidities), acuity (e.g., organ dysfunction, mechanical ventilation), length of stay, and discharge disposition (e.g., SNF, rehabilitation, home) between study groups. Comparisons of the two groups will be made using univariate analyses such as the *t* test and chi-square test.

The primary composite outcome, 30-day readmission and mortality, will be compared between the two arms using logistic regression. We will present the effects of the STAR program on the incidence of the composite readmission and mortality outcome as odds ratios and 95% confidence intervals. In addition to the primary intent-to-treat analysis, and since there is significant overlap between general AH Transition Services and the STAR program services integrated within AH Transition Services, we will conduct a modified intent-to-treat analysis excluding usual care patients who attended the AH Transition Services clinic during the 30 days after hospital discharge. Based on historical data, we anticipate an approximately 10% referral rate to AH Transition Services in the usual care group. Finally, we will complete a per-protocol analysis to compare patients in the STAR intervention arm who are eligible at hospital discharge and complete the 30-day STAR program to patients who are eligible at hospital discharge and receive usual care.

Secondary acute care and cost outcomes and process measures will be evaluated using the same approach. We will test different distribution parameters to determine the optimal distribution family for each model and outcome variable (e.g., gamma distribution for costs, Poisson distribution for acute care-free days). Any substantial changes to the study processes will be documented, discussed with investigators at monthly meetings, and incorporated into analyses of study outcomes. All hypothesis tests will be two sided and data will be analyzed using SAS Enterprise Guide v7.1 (Cary, NC, USA).

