### Risk scoring and recruitment

Separate risk prediction scores are applied to assess 30-day hospital readmission and 30-day mortality using previously developed logistic regression models. Each model is derived from readily captured variables collected as part of routine clinical care during the first 24 h after ED presentation, such as physiologic measurements, laboratory values, basic sociodemographic characteristics, and personal medical history [31]. All model covariates are sourced from a patient’s clinical data during hospitalization and billing history at the time of hospital admission for near real-time application. Model performance was determined using 10-fold cross-validation (30-day mortality model discrimination: area under the receiver operator characteristic curve (AUC) = 0.85, negative predictive value (NPV) = 0.97; 30-day readmission model discrimination: AUC = 0.70, NPV = 0.89). High-risk features included older age, higher number of comorbidities (Charlson Comorbidity Index), hospital admission within the last 90 days, chemotherapy receipt within the last 90 days, respiratory agent receipt within the last 90 days, hyperlactatemia, hypotension, leukocytosis, and tachypnea. Risk probabilities between 0 and 1 are assigned to hospitalized patients for each outcome.

Each weekday (i.e., Monday–Friday), we generate an automated list of eligible patients at high risk for 30-day mortality or readmission, as identified by our previously developed risk models. Patients are randomly assigned to STAR or usual care arms. For those patients allocated to receive care via STAR, their information is sent by secure e-mail to the STAR navigator. For patients in both arms, data from the automated, daily patient list are sent to the study database for tracking via a computer-based process. At any point, patients may decline participation in STAR or any components of usual care.

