### Sample size calculation

This study is designed to detect a 25% relative reduction in the primary outcome, the composite rate of 30-day readmission and mortality, which is reasonable given prior literature suggesting that between 22% and 42% of hospital readmissions after sepsis are preventable, including data from a secondary analysis of the subgroup of sepsis patients in our previous transitions of care trial (relative risk = 0.49, 0.24–0.97) [33]. Based on the historical data, the control group is estimated to have a 40% combined readmission and mortality rate. Group sample sizes of 354 in the STAR group and 354 in the usual care group achieve 80% power (α = 0.05) to detect a 10% absolute reduction between the group proportions (i.e., 25% relative reduction). Under the alternative hypothesis, the proportion in the STAR group is assumed to be 30%.

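### The primary logistic regression could prespecify the pre-randomisation risk scores for a modest gain in power, and length of stay and discharge disposition are wrongly listed as baseline covariates

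*Protocol article*

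**What the plan says.** Statistical analysis: the 30-day composite "will be compared between the two arms using logistic regression", with effects given as odds ratios and 95% confidence intervals. No covariate is named, and the model is not called unadjusted.

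Risk scoring and recruitment: "Risk probabilities between 0 and 1 are assigned to hospitalized patients for each outcome". The outcomes are 30-day readmission and 30-day mortality, and the inputs come from the first 24 hours after arrival in the emergency department. The stated AUCs are 0.70 for readmission and 0.85 for mortality. The same scores decide eligibility (readmission risk of at least 20% or mortality risk of at least 10%), so they exist before randomisation.

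Statistical analysis, balance check: the variables introduced as baseline covariates end with "length of stay, and discharge disposition (e.g., SNF, rehabilitation, home) between study groups".

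Sample size calculation: 354 per arm "achieve 80% power (α = 0.05) to detect a 10% absolute reduction between the group proportions", where "the control group is estimated to have a 40% combined readmission and mortality rate" and the STAR rate is assumed to be 30%. The Statistical analysis section adds that "All hypothesis tests will be two sided".

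**The concern.** Two matters arise.

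First, the trial computes for each patient two scores that predict the components of its own primary outcome. They are fixed before randomisation and needed for eligibility, so they should be virtually complete. The Treatment allocation section describes no stratification by risk or hospital. A model without the scores forgoes some precision and leaves any chance difference in risk between the arms uncorrected in the estimate. The reported measure also matters: the trial was sized on a risk difference, and adjustment changes what the odds ratio means.

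Second, length of stay and discharge disposition are not known at randomisation. A difference between arms in either may be an effect of STAR, yet under the present label it would be read as a failure of randomisation. If anyone later adjusted for such a difference, the model would condition on a consequence of treatment.

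**Working it through.** **1. The plan's own figure.** Inputs from the Sample size calculation: p1 = 0.40, p2 = 0.30, two-sided alpha 0.05, power 0.80.

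- Unpooled variance: n = (1.960 + 0.842)² × (0.40×0.60 + 0.30×0.70) / 0.10² = 7.849 × 0.45 / 0.01 = 353.2, so 354 per arm. This is the stated size.
- Pooled variance: n = [1.960 × √(2×0.35×0.65) + 0.842 × √0.45]² / 0.10² = 355.9, so 356 per arm.
- Power with 354 per arm (pooled variance under the null): 79.8%.

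The size is that of a comparison of two proportions without covariates, and an unadjusted analysis delivers the planned power.

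**2. What adjustment would add.** Simulated trials had 354 patients per arm, marginal risks of 40% and 30%, and one normally distributed score on the logit scale. The score's slope was set to give the assumed AUC for the composite. Each trial was analysed by logistic regression with and without the score (Wald test, 10,000 trials per row). The AUC is an assumption: the article gives none for the composite among enrolled patients.

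| Assumed AUC | Power, unadjusted | Power, adjusted | Gain (points) | Conditional odds ratio |
|---|---|---|---|---|
| 0.55 | 80.6% | 80.5% | about 0 | 0.641 |
| 0.60 | 79.6% | 80.5% | 0.9 | 0.635 |
| 0.65 | 80.7% | 82.9% | 2.2 | 0.624 |
| 0.70 | 80.1% | 84.6% | 4.4 | 0.607 |
| 0.75 | 79.6% | 86.7% | 7.1 | 0.584 |

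Gains are taken from unrounded power. The simulation standard error of each power is about √(0.8×0.2/10,000) = 0.4 points. A separate simulation of 3,000 trials per row agrees: 79.5% to 81.5% at AUC 0.645, and 79.2% to 83.6% at AUC 0.701.

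The upper rows are less plausible. The stated AUCs are for the two outcomes separately, and selecting patients on the same scores narrows their range among those enrolled. Hospital was not simulated.

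**3. Effect measures at the design values.**

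- Risk difference: 0.30 − 0.40 = −0.10.
- Risk ratio: 0.30/0.40 = 0.75, the 25% relative reduction.
- Marginal odds ratio: (0.30/0.70)/(0.40/0.60) = 0.643.

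The last column of the table shows the odds ratio moving from 0.643 towards 0.584 on adjustment, although the marginal risks stay at 40% and 30%. This is non-collapsibility. The risk difference and risk ratio, standardised over the trial population, remain on the scale of the design target.

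**4. Timing of the two listed variables.**

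- Study setting and population: patients must still be in hospital when the daily list is drawn, so randomisation precedes discharge.
- Trial interventions: the navigator's first contact is during the stay. Before discharge the navigator prompts physical therapy, antibiotic stewardship and palliative care consultations, and follows discharge planning every 24–48 h.
- Study outcomes: discharge to hospice is itself measured as an indicator of end-of-life care. It is also a discharge disposition, so the article treats the same kind of variable as a result in one section and as baseline in another.
- Study outcomes: deaths count from index presentation. For a patient who dies in the index stay, length of stay and disposition are fixed by a primary-outcome event.

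Both variables are therefore post-randomisation.

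**The case against.** The strongest reply is that the covariate point rests on silence. A journal article commonly leaves the covariate list to the analysis plan, which is not shown. That stands: the absence of a list is not an error, and a reader should not infer that the model is fixed as unadjusted. The point is a recommendation to use data the trial already holds.

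A reader might also infer that the trial loses power. It does not: the planned power is reached without adjustment, and what is forgone is an optional gain that could be close to nil. An unadjusted analysis is valid, and its type I error and confidence interval already allow for chance imbalance.

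A third tempting reading is that the plan will adjust for length of stay and disposition. The text provides only for a balance check by univariate tests. No sentence brings either variable into the outcome model, and the patient-characteristics table (Table 2) lists neither. The mislabelling itself remains.

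Nor should one conclude that the odds ratio hides the absolute effect. Table 3 has a column for each arm, so crude risks can be read beside it, and 0.643 corresponds exactly to 40% v 30%. However, once the model is adjusted, that correspondence no longer holds for the conditional odds ratio.

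Finally, adjustment is not free of any drawback, because it changes the meaning of the odds ratio. That drawback is small and is met by reporting standardised measures.

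**Conclusion.** The point holds in two limited parts.

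Prespecified adjustment for the two risk scores and hospital is a better use of data already collected. The gain is about 0 to 5 percentage points of power for an assumed AUC of 0.55 to 0.70, with some protection against chance imbalance in risk. The size rests on the design rates, 354 analysed patients per arm, a single score on the logit scale, and an AUC that the article does not give. It is an improvement to a plan that already meets its stated power.

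Calling length of stay and discharge disposition baseline covariates is wrong as written, and this needs no assumption beyond the article's own timing of randomisation and of STAR. No effect on the primary result is shown, because no adjustment for them is planned.

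**What to change.** Before outcome data are seen, state in the protocol or analysis plan:

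1. The primary logistic model contains arm, the logit of the readmission score, the logit of the mortality score (both as held at randomisation) and hospital.
2. The standardised marginal risk difference and risk ratio are reported with 95% intervals beside the odds ratio, which is labelled conditional.
3. The model with arm alone is kept as a sensitivity analysis.
4. Length of stay and discharge disposition are removed from the baseline list, described as post-randomisation measures, and will not enter the primary model.

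If the existing analysis plan already fixes items 1 to 3, only item 4 remains. The cost is wording and a few lines of analysis code, with no new data and no change to the sample size. The one price is that the adjusted odds ratio is no longer directly comparable with the 0.643 implied by the design, which item 2 addresses.

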
After discharge, the STAR navigator follows patients regardless of the discharge location (e.g., home, SNF) and remotely monitors via EHR-based and telephone-based review throughout the 30 days post hospital discharge (Fig. 2). Specifically, the STAR navigator provides telehealth monitoring at < 48 h, 72–96 h, and 7–10 days post discharge. Within 24–48 h of hospital discharge, the STAR navigator contacts the patient or caregiver for initial post-discharge medication reconciliation, with a review by the AH Transition Services pharmacist and confirmation that the patient has filled or received all medications needed. The STAR navigator coordinates with the patient’s primary care provider or AH Transition Services to address any outstanding medication needs. Also at this touchpoint, the STAR navigator monitors for fever (> 38 °C after recheck), new or worsening symptoms (e.g., dyspnea, diarrhea, or redness, swelling, or pain (for skin and soft tissue infection)), and new limitations in functional status (e.g., not out of bed, not eating). Concerns identified through proactive monitoring prompt a primary care provider contact for follow-up within 24 h. If the primary care provider cannot be reached after one attempt, the navigator contacts AH Transition Services to coordinate either a virtual visit with a physician facilitated by community paramedicine or an in-person physician visit [32]. The STAR navigator also meets at least weekly with the AH Transition Services Medical Director to review ongoing cases and coordinate additional support as needed. Additional touchpoints at 72–96 h and 7–10 days post discharge include similar elements (i.e., medication reconciliation, targeted symptom monitoring, vitals and weight checks, confirmation that the patient can make scheduled outpatient appointments) and response (i.e., coordinating follow-up with primary care or AH Transition Services within 24 h for concerning issues). If a provider visit has been completed, the STAR navigator reviews any visit notes, available laboratory values (e.g., complete blood count, basic metabolic panel), and documented therapy plan. After the first 10 days following hospital discharge, the STAR navigator maintains weekly telehealth touchpoints with patients who remain at high risk for poor outcome, defined as any previous positive screen or high-risk comorbid condition (e.g., chronic lung disease, heart failure) [10, 38–40]; and one additional third-week touchpoint with patients considered low risk after the first 10 days post discharge. Each of these post-acute touchpoints include targeted symptom monitoring, vitals and weight check, and escalation to an additional outpatient provider visit within 24 h if there are concerns. Any identified concerns again prompt an attempt to contact the primary care provider followed by AH Transition Services. The STAR program intervention completes 30 days post hospital discharge.

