### Study outcomes

The primary outcome is a composite, dichotomous endpoint of all-cause mortality or unplanned hospital readmission assessed 30 days post index hospital discharge (Table 3). This combined outcome is ideally suited to our pragmatic study design because the elements are uniformly captured from data contained in the AH EDW, minimizing non-differential assessment, outcome misclassification, and missing data. Additionally, mortality and hospital readmission are widely regarded as patient-centered outcomes, and rates for both adverse outcomes remain high after sepsis hospitalization [43–45]. Finally, readmission rates have recently declined secondary to focused initiatives [46]. However, some data suggest increased mortality during the same interval [47], indicating the importance of measuring mortality and readmission rates in combination. Mortality is defined as any date of death documented in the AH EDW from index hospital presentation to within 30 days of index hospital discharge, including events from national death record data fed monthly into the EDW [48]. Readmission is defined as any unplanned inpatient or observation encounter to any of 47 AH hospitals within the 30 days following index hospital discharge. Both inpatient and observation status hospitalizations count toward the readmission outcome, because either status represents an adverse event important to patients and healthcare systems. This information is captured from encounter data in the AH EDW and has been previously extracted by the study team.

**Table 3 Tab3:** IMPACTS primary and secondary outcomes

Clinical and cost outcomes	Usual care (*n* =)	STAR program (*n* =)
Primary outcome		
30-day all-cause mortality or hospital readmission	–	–
Secondary outcomes		
30-day all-cause mortality	–	–
30-day hospital readmission	–	–
30-day sepsis/infection-related hospital readmission	–	–
30-day chronic lung disease-related hospital readmission	–	–
30-day heart failure-related hospital readmission	–	–
30-day acute renal failure-related hospital readmission	–	–
30-day emergency department visits	–	–
30-day acute care-free days alive	–	–
30-day acute care costs	–	–
30-day total healthcare costs^a^	–	–
90-day all-cause mortality	–	–
90-day hospital readmission	–	–
90-day sepsis/infection-related hospital readmission	–	–
90-day chronic lung disease-related hospital readmission	–	–
90-day heart failure-related hospital readmission	–	–

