To provide additional context to understanding STAR implementation, important process measures are tracked in both groups, including: functional assessment or physical therapy consult [49, 50]; mental health assessment by PHQ-2 or PHQ-9 [51]; referrals to physical therapy or outpatient rehabilitation, speech therapy, and behavioral health [52–55]; early outpatient follow-up (i.e., completed outpatient primary care follow-up (or attendance at an AH Transition Services clinic) within 7 days of discharge) [56–60]; and documented medication reconciliation in the EHR during the 30 days post discharge [61, 62]. Because sepsis may occur in the setting of long-standing illness and declining health [63–65], we also measure the quality of end-of-life care, including place of death (i.e., hospital or other location) and the proportion of patients who received a palliative care consult, completed care preferences documentation, and were discharged to a hospice.

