We intentionally developed broad infection criteria to initially define adults with suspected serious infection or sepsis, with the additional application of our high-performing risk stratification models to objectively narrow the population to those at the highest risk of poor outcomes and with the potential to benefit most from added support. We anticipate that this approach will include a representative sample of patients with different chronic and acute problems. Because of the expected heterogeneity, we have defined a priori several subgroups of interest to further evaluate possible differential effects of the STAR program (e.g., patients with high comorbidity burden).

There are some limitations to this study. The results may not be generalizable to all sepsis survivors because study participants are enrolled from a single healthcare system. However, the inclusion of three heterogeneous hospitals within the healthcare system increases the applicability of our findings. Second, we did not protocolize the usual care arm, thus care provided to patients in this group may be variable or change over time. While this may increase noise in determining the true treatment effect, it is consistent with the concept of a pragmatic study design. The STAR program was developed in partnership with a multidisciplinary team of sepsis stakeholders and designed to be implemented and evaluated in a real-world setting. If effective, this program would offer a timely solution for hospitals facing potential financial penalties for higher-than-expected readmission rates and looming alternate payment models such as bundled payments and shared savings programs for Accountable Care Organizations, which creates incentives to deliver care in less intensive settings during the 90 days after hospitalization.

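### The supplementary modified intent-to-treat analysis removes clinic attendees from usual care only, after randomization and inside the outcome window, so it is not a randomized comparison and may be biased in either direction

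*Protocol article*

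**What the plan says.** The Statistical analysis section makes the intent-to-treat comparison primary, after removing patients whose infection was ruled out. It then adds a modified intent-to-treat analysis "excluding usual care patients who attended the AH Transition Services clinic during the 30 days after hospital discharge". The reason given is that "there is significant overlap between general AH Transition Services and the STAR program services integrated within AH Transition Services". On scale, the section says only that "we anticipate an approximately 10% referral rate to AH Transition Services in the usual care group". It describes no weighting, adjustment, landmark or caveat for this analysis.

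Three other places bear on it:

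- **Study outcomes.** The primary composite is "all-cause mortality or unplanned hospital readmission assessed 30 days post index hospital discharge", and deaths count "from index hospital presentation to within 30 days of index hospital discharge". The same section tracks early follow-up in both groups as a process measure. One way to meet it is "attendance at an AH Transition Services clinic" within 7 days of discharge.
- **Trial interventions.** STAR patients can be routed to the same service: if primary care cannot be reached, "the navigator contacts AH Transition Services to coordinate either a virtual visit with a physician facilitated by community paramedicine or an in-person physician visit". Transitional care arranged according to a patient's needs is listed among the typical elements of usual care.
- **Discussion.** The authors state that "we did not protocolize the usual care arm".

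**The concern.** Clinic attendance is not a baseline characteristic. It happens after randomization and in the same 30 days as the outcome, and whether it happens depends on prognosis in two opposing ways.

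- A patient who dies during the index stay is an event and can never attend, so can never be removed. Early death after discharge also prevents attendance. This removes relatively more survivors from usual care, raises the remaining event rate and favours STAR.
- Referral according to need can send sicker patients to the clinic, and a patient can attend after a readmission. This removes events from usual care and works against STAR.

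The STAR arm has no matching exclusion, so nothing offsets the shift. The rule also removes people who received an ordinary part of unprotocolized usual care, so what remains is not the comparator that the trial defines. At stake is how the result is read. Under an intent-to-treat name, it could be taken as the effect of STAR free of overlap, which deleting patients from one arm does not estimate.

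**Working it through.** **Inputs from the article**

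- Composite rate 40% in usual care and 30% in STAR, 354 per arm, 80% power, α = 0.05 (Sample size calculation).
- Two-sided tests, and about 10% referral in usual care (Statistical analysis).

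**Inputs assumed, because the article gives none**

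- Share of usual care removed, f: 5% or 10%. The 10% takes every referred patient as an attendee; the 5% takes half of them.
- Event rate among those removed, q: 10% to 60%.

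**Step 1: the plan's own figure.** With unpooled variance, n = (1.960 + 0.842)² × (0.40 × 0.60 + 0.30 × 0.70) / 0.10² = 353.2, so 354 per arm. The pooled formula gives 356, and power at 354 is 79.8%. The stated sample size reproduces.

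**Step 2: usual care rate after the exclusion.** Rate = (0.40 − f × q) / (1 − f).

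- f = 0.10, q = 0.10: (0.40 − 0.01) / 0.90 = 0.4333
- f = 0.10, q = 0.60: (0.40 − 0.06) / 0.90 = 0.3778
- f = 0.05, q = 0.10: (0.40 − 0.005) / 0.95 = 0.4158

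**Step 3: odds ratio with no true effect.** STAR stays at 40%, with odds 0.40 / 0.60 = 0.667. For f = q = 0.10 the usual care odds are 0.4333 / 0.5667 = 0.765, so OR = 0.667 / 0.765 = 0.87. Without the exclusion, OR = 1.00.

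**Step 4: rejection rate with no true effect.** This is a two-sided pooled z test with 354 in STAR and 354 × (1 − f) in usual care, that is, about 336 or 319. For f = q = 0.10 the shift is 0.0333, the standard error about 0.0381 and the critical difference 1.96 × 0.0381 = 0.0746. Rejection is Φ((0.0333 − 0.0746) / 0.0381) + Φ((−0.0333 − 0.0746) / 0.0381) ≈ 0.139 + 0.002 = 0.141.

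**Results.** The OR under the design alternative, 30% vs 40%, is 0.643 without the exclusion.

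| Removed (f) | Attendee rate (q) | Remaining usual care rate | Shift (points) | OR, no effect | OR, design effect | Rejection, no effect |
|---|---|---|---|---|---|---|
| 5% | 10% | 41.58% | +1.58 | 0.937 | 0.602 | 7.1% |
| 5% | 20% | 41.05% | +1.05 | 0.957 | 0.615 | 5.9% |
| 5% | 40% | 40.00% | 0 | 1.000 | 0.643 | 5.0% |
| 5% | 60% | 38.95% | −1.05 | 1.045 | 0.672 | 5.9% |
| 10% | 10% | 43.33% | +3.33 | 0.872 | 0.560 | 14.1% |
| 10% | 20% | 42.22% | +2.22 | 0.912 | 0.586 | 9.0% |
| 10% | 40% | 40.00% | 0 | 1.000 | 0.643 | 5.0% |
| 10% | 60% | 37.78% | −2.22 | 1.098 | 0.706 | 9.1% |

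The exclusion is neutral only where attendees share the arm's 40% rate. The assumed range reaches further below 40% than above it, so its larger positive end is not evidence that the bias favours STAR. At q = 70% and f = 10% the shift would be −3.33 points.

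**The case against.** The strongest defence is that this analysis is supplementary. The article adds it to a primary intent-to-treat comparison that keeps attendees in the arm to which they were randomized, and neither the hypothesis nor the sample size depends on it. That stands and limits the seriousness of the point. A reader might infer that the trial's own error rate or main result is compromised; nothing in the article supports that.

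The asymmetry also has a stated purpose. STAR sits within Transition Services, so use of the service is assigned care in one arm and overlap in the other. That explains the rule but does not remove the selection it causes.

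The size is uncertain too. The 10% is a referral rate while the rule acts on attendance, and the attendee event rates are assumed. At 5% removed, the shift is about 1 to 1.6 points and rejection 6 to 7%. The 14% figure needs all referred patients to attend and to have a quarter of the arm's event rate. That also stands, so the size is given as a range.

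Two further inferences are tempting but go too far. One is that attendees must have stayed out of hospital, so that the bias must favour STAR. The window is 30 days and a readmitted patient can attend later; discharge alive is the only strict requirement. The other is that the protocol classes clinic attendance as a mark of good care. It lists attendance within 7 days as one way to meet a process measure, tracked for context.

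**Conclusion.** The concern holds for the supplementary analysis only. A rule that removes patients from one arm, on an event after randomization and within the outcome window, does not leave a randomized comparison, and nothing else in the article corrects this. The intent-to-treat label is therefore wrong.

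The bias may go in either direction, and its sign cannot be determined from the article. Over the stated assumptions it amounts to about −2.2 to +3.3 points in the usual care rate, against a design difference of 10 points. That corresponds to a null odds ratio of 0.87 to 1.10 and a false-positive rate for this one test of up to about 14%. It is zero if attendees happen to have the arm's event rate. These shifts are measured against STAR versus usual care as delivered. If the clinic itself lowers events, part of a low attendee rate would be its effect, and deleting attendees cannot separate that from selection.

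**What to change.** Drop the one-arm exclusion. Keep all randomized usual care patients in the comparison, subject to the infection rule-out that already applies to both arms, and report Transition Services attendance by arm over the 30 days. Early attendance is already tracked in both groups, and the planned exclusion would itself need 30-day attendance in usual care, so little new data work is involved.

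If an overlap analysis is kept:

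- stop calling it intent-to-treat;
- label it exploratory and non-randomized, and state the selection problem beside the result;
- preferably restrict both arms by a probability of referral predicted only from pre-randomization data, which keeps the comparison randomized within the restricted set.

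The cost is a change of wording and, for the restricted version, one prediction model. The trial gives up a simple no-overlap estimate or accepts a less precise one. Censoring usual care patients at first attendance with inverse-probability weights is possible but not required: it would replace the dichotomous endpoint with a time-to-event one and need a rule for deaths during the index stay.

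### The supplementary per-protocol analysis removes post-discharge deaths from the STAR arm but keeps them in usual care, which tends to bias it toward benefit

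*Protocol article*

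**What the plan says.** All references are to the protocol article.

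- **Statistical analysis, primary.** "Primary analyses will follow an intent-to-treat approach", after exclusion of patients whose infection was ruled out. The composite "will be compared between the two arms using logistic regression".
- **Statistical analysis, per-protocol.** After the intent-to-treat and a modified intent-to-treat analysis, a third analysis will "compare patients in the STAR intervention arm who are eligible at hospital discharge and complete the 30-day STAR program". The comparison set is fixed only by the words "to patients who are eligible at hospital discharge and receive usual care".
- **Trial interventions.** "The STAR program intervention completes 30 days post hospital discharge". Touchpoints continue after day 10: weekly for patients still at high risk, and one in the third week for the others.
- **Study outcomes.** The primary outcome is a "composite, dichotomous endpoint of all-cause mortality or unplanned hospital readmission assessed 30 days post index hospital discharge". Deaths count "from index hospital presentation to within 30 days of index hospital discharge".

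The Statistical analysis section gives no landmark, no matching condition for usual care and no adjustment for this comparison. It does not say whether a readmitted patient can still count as a completer.

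**The concern.** Completion can be established only at day 30, when the outcome window closes. A STAR patient who dies on day 12 has had a primary outcome event and, on the plain wording, has not completed. That patient leaves the STAR set. A usual-care patient who dies on day 12 stays in and counts as an event. Membership of one arm's set therefore depends on part of the outcome, and membership of the other does not. This is immortal-time selection.

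It differs from ordinary adherence selection, where completers differ from non-completers in prognosis and covariate adjustment may help. Here the events themselves are deleted by definition, and adjustment cannot bring them back.

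What is at stake is interpretation. If the intent-to-treat result were null, a favourable per-protocol odds ratio beside it could be read as evidence that the program works in those who receive it in full, when part or all of the difference could come from how the set was built.

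**Working it through.** **The plan's own figure.** Sample size calculation gives 354 per arm for 40% v 30%, 80% power, α = 0.05; Statistical analysis makes tests two-sided. With unpooled variances, n = (1.960 + 0.842)² × (0.40×0.60 + 0.30×0.70) / 0.10² = 353.2, which rounds up to 354. The figure reproduces.

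**Inputs.** From the documents: control composite 40% and 354 per arm. Not in the documents, and so assumed: *d*, the share of patients who die after discharge within 30 days (the 40% is not split into its components); *f*, the share of readmitted survivors who do not complete; *w*, the share of event-free STAR patients who do not complete. For simplicity, 40% is taken as the composite rate among patients eligible at discharge.

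**Null model.** Both arms have a true composite of 0.40. Usual care keeps everyone, so its rate is 0.40. With w = 0, the STAR per-protocol set has

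- share kept = 1 − d − (0.40 − d)f
- event rate = (0.40 − d)(1 − f) / [1 − d − (0.40 − d)f]

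**Deaths only (f = 0).** The rate is (0.40 − d)/(1 − d). The chance of a false significant benefit comes from a two-proportion z test, 354 v 354 × share kept.

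| d | STAR kept | STAR rate | Difference from 40% | OR | False significant benefit |
|---|---|---|---|---|---|
| 3% | 343 | 0.37/0.97 = 38.1% | 1.9 points | 0.93 | 7% |
| 5% | 336 | 0.35/0.95 = 36.8% | 3.2 points | 0.88 | 13% |
| 8% | 326 | 0.32/0.92 = 34.8% | 5.2 points | 0.80 | 29% |
| 10% | 319 | 0.30/0.90 = 33.3% | 6.7 points | 0.75 | 43% |

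The nominal rate in that direction is 2.5%. Simulation (20,000 trials per scenario) gives 13% at d = 5% and 44% at d = 10%.

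**If a quarter of readmitted survivors also do not complete (f = 0.25).** At d = 8%: 0.32 × 0.75 / (0.92 − 0.32 × 0.25) = 0.24/0.84 = 28.6%. At d = 10%: 0.30 × 0.75 / (0.90 − 0.30 × 0.25) = 0.225/0.825 = 27.3%. The false differences are 11.4 and 12.7 points, with false significance about 87% and 93%.

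**The opposing force (w > 0).** Dropping event-free STAR patients raises the STAR rate. The composite returns to 40% when w = 1 − (0.40 − d)(1 − f)/0.40. With f = 0 this is 12.5% at d = 5%, 20% at d = 8% and 25% at d = 10%. With f = 0.25 it is 40% at d = 8% and about 44% at d = 10%.

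**Mortality.** STAR post-discharge deaths in the per-protocol set number zero for every d, f and w. No value of w changes that.

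**The case against.** Four points can be made for the plan.

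1. *It is a supplementary analysis.* This stands. Intent-to-treat is primary, the sample size does not rest on the per-protocol set, and no text ties the conclusions to it. A reader might infer that the trial's main answer is compromised; the documents do not support that.

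2. *Completion is not given an operational rule.* Risk scoring and recruitment lets patients decline STAR, so the phrase may have been meant to separate participants from refusers, and an analysis plan could define it by contacts due while alive. That would remove the survival condition. But the article fixes both sets, and its words, read with the program's day-30 end, require survival to day 30. The criticism is of that wording, not of an analysis already run.

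3. *The size, and for the composite even the net direction, depends on unknowns.* This also stands. A reader might infer that the analysis will show a benefit whenever there is none. With deaths only and d = 3% to 10%, a null trial fails to show a significant benefit 93% to 57% of the time. Event-free non-completion of about 20% to 25% would cancel the deaths-only bias at d = 8% to 10%. Such cancellation would be luck, and it never reaches mortality.

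4. *Readmission need not end the program.* The navigator follows patients through day 30 wherever they are discharged to, and also works with inpatients. No text makes readmission a non-completion, so the 11 to 13 point figures illustrate an assumption. With deaths only and d up to 10%, the false difference stays below the 10-point design effect.

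**Conclusion.** The concern holds for the per-protocol analysis as worded. It conditions the STAR arm alone on reaching the end of the outcome window, so STAR post-discharge deaths are removed and usual-care deaths are kept. Two consequences differ in certainty:

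- STAR post-discharge 30-day mortality is zero by construction, whatever the assumptions. All-cause 30-day mortality is also a listed secondary outcome.
- The composite tends to be biased toward benefit. With deaths only, the bias is about 2 to 7 points for d = 3% to 10%. It would be larger if readmitted patients also drop out, and smaller or reversed if enough event-free patients do not complete.

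These sizes rest on assumed values of d, f and w. If in-hospital deaths were kept in the usual-care set, the imbalance would be larger. The intent-to-treat primary analysis is unaffected. This should be fixed, at the weight of a supplementary analysis.

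**What to change.** In Statistical analysis, replace the completion condition. Define the STAR per-protocol set by adherence to STAR touchpoints that fell due before day 30 while the patient was alive and not readmitted. Patients with early events then stay in, judged on the contacts due up to the event. Compare them with usual-care patients eligible at discharge, adjusted for baseline risk, and state that in-hospital deaths are handled identically in both sets.

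A complier-average effect in all randomised eligible patients may be added as an option. It answers a somewhat different question, and if treatment received meant any navigator contact it could lie close to intent-to-treat, so it need not replace the per-protocol analysis.

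The cost is a few lines of text and a little more analysis work. Data collection already has completed STAR workflow steps exported to REDCap. The estimate will probably look less favourable to STAR. A residual limit remains: a patient with an early event has fewer touchpoints to miss and so qualifies more easily, so the result should still be reported as supportive only.
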